### Power calculation

Data from CHIP interventions conducted in Australia and New Zealand [20] were used for the power analyses. Power calculations were conducted on all the biometrics to be measured in the present study, which indicated that of all the biometrics, detecting a significant change in triglycerides would require the greatest sample size. Using an estimated mean baseline triglyceride level of 1.15 mmol/L with a standard deviation of 0.33 mmol/L, to achieve a 5 % level of significance with 80 % power will require 87 participants in each of the three countries. Allowing for a 10 % loss to follow up at 6 months, in each country a total of 96 participants will be recruited, constituting two intervention villages each with 24 participants and two control villages each with 24 participants. In total, 288 participants from the three countries will be involved in the study: 144 intervention and 144 control.

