### Outcome measures

Data on biometrics, blood measures and health behaviour will be collected on individuals in the intervention and control villages at program entry (baseline), one month, three months and six months by a team of HP’s. A medical assessment, including personal and family health history will be collected at program entry only. The following measurements will be collected:Height, weight, body mass index (BMI), waist circumference and blood pressure will be measured on site by a HP. Weight (in light clothing with shoes removed), to determine BMI, will be measured by a HP, following 12 h fast using commercial weight scales. Blood pressure will be measured using a medical sphygmomanometer by a HP. Measurements will be repeated at each time point using the same equipment to reduce systematic measurement error.Fasting lipid profile and plasma glucose will be drawn on site. Whole blood samples will be collected into capillary and heparinised tubes by the designated HP following via finger prick method. Samples will be removed from the tube for analysis, using the CardioChek PA portable blood analyser within 5 min of the blood draw. All alcohol swabs, lancets, used blood tubes and CardioChek pads will be deposited in biohazard material bags and taken by the HP to the local pathology laboratory or public hospital for incineration.Physical activity will be quantified using a pedometer supplied to the participants who will record their daily steps taken in a log book provided. For illiterate participants, the final reading at the end of each day will be recorded by someone with literacy skills from the same village.Health related behaviours will be assessed using a lifestyle questionnaire administered verbally by the HP (requirement due to the relatively low levels of literacy of the participants). A medical doctor or nurse will be present at the beginning of the project to collect and record information in private. The information will then be given to the ADRA supervisor who will keep it in a locked file.Lifestyle habits include: smoking, alcohol, kava and betel nut usage; frequency of daily consumption of limited key foods including, fruit and vegetables, fatty and processed foods, meat and wholegrains/cereals; frequency of weekly light, moderate and strenuous physical activitySubjective wellbeing include: emotional health, supportive relationshipMedical history, including personal and family history of heart problems, high blood pressure and blood glucose, cancer and breathing problems.Medication usage. During the initial medical assessment, the participants will present all medications they are taking and the type and dosage will be recorded by the HP.

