### Statistical methods

The (biomedical) data will be analysed using IBM™ Statistics (version 21). Continuous data will be expressed as number, mean, standard deviation (SD). Categorical data will be summarized as counts and percentages. For each country, differences between participants in the intervention and control groups at baseline will be examined using Chi square for categorical variables and independent samples t-tests for continuous variables. The extent of changes (percent, and mean with 95 % confidence intervals (CI)) from baseline, one month, three months and six months will be assessed using Analysis of Variance (repeated measures). For all analyses, results are considered significant at *P* < 0.05.

The qualitative data obtained through the various participatory, qualitative techniques listed above, will first be checked for accuracy with some of the participants and then with program staff (facilitators and supervisor). For the analysis, focus group data from the first village will be broken down into parts and examined for emergent categories (themes or patterns) and sub-categories, then coded. These categories and sub-categories may at this stage start to show a theory. Coding of the second focus groups will be done with the first in mind. Subsequent focus group discussion in the other two countries will also be coded with the emerging theory in mind.

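### Repeated-measures ANOVA conventionally drops anyone missing one of four visits, while the sample size allows only for 10% loss at 6 months; a mixed model with a village effect would keep those data

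*Protocol article*

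**What the plan says.** All participants are to be assessed four times, "at program entry (baseline), one month, three months and six months by a team of HP’s" (Outcome measures). The Statistical methods section fixes the analysis of these data: in a named package, the extent of change "from baseline, one month, three months and six months will be assessed using Analysis of Variance (repeated measures"). It names no alternative model, no handling of missed visits and no term for village.

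The Power calculation section takes triglycerides as the measure needing the largest sample. From an "estimated mean baseline triglyceride level of 1.15 mmol/L with a standard deviation of 0.33 mmol/L", it states that "to achieve a 5 % level of significance with 80 % power will require 87 participants in each of the three countries". It then continues: "Allowing for a 10 % loss to follow up at 6 months, in each country a total of 96 participants will be recruited". The total is "288 participants from the three countries will be involved in the study: 144 intervention and 144 control". The loss allowance refers to the 6-month visit alone.

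The Study design section makes the village the unit of randomisation, with six villages per arm.

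**The concern.** Conventional repeated-measures ANOVA needs a complete row of visits for each participant. A person measured at baseline, 3 months and 6 months but absent at 30 days contributes nothing. A person lost between 3 and 6 months is also removed from the earlier comparisons, although three of that person's four visits exist. The sample size was inflated as if the only way to leave the analysis were to be missing at 6 months.

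Two things are at stake. Precision may fall below what was planned. The result would also rest on a subset whose representativeness has to be assumed: a complete-case analysis is safe when the excluded people are, within arm, like those kept, and it can mislead when exclusion is related to how a participant's measurements are changing.

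**Working it through.** **Inputs.** From the Power calculation section: 87 required per country, 10% loss at 6 months, 96 recruited per country, 288 in all, SD 0.33 mmol/L, 5% significance, 80% power. From Outcome measures: four visits, two of them interim. Not given: the rate of missed interim visits, so a range is assumed.

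**The plan's own inflation.** 87 × 1.10 = 95.7, rounded to 96; dividing instead gives 87 / 0.90 = 96.7, rounded to 97. The stated 96 agrees with the first and is one short of the second. Working back, 96 × 0.90 = 86.4, already marginally under 87, so there is no spare capacity for any other loss.

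**Loss that follows from the plan's own 10%.** 288 × 0.10 = 28.8, about 29 people without a 6-month value. Conventional repeated-measures ANOVA removes them from the 30-day and 3-month comparisons as well, whether or not they were measured at those visits.

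**Further loss if interim visits are missed.** Let m be the share absent at each interim visit, taken as independent between visits and of 6-month loss. Complete cases per country = 96 × 0.90 × (1 − m)². Recruitment needed to keep 87 complete = 87 / [0.90 × (1 − m)²], rounded up.

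| m (assumed) | Share complete | Complete per country (87 required) | Complete overall (3 × 87 = 261) | Recruitment needed per country |
|---|---|---|---|---|
| 0% | 90.0% | 86.4 | 259.2 | 97 |
| 3% | 84.7% | 81.3 | 243.9 | 103 |
| 5% | 81.2% | 78.0 | 233.9 | 108 |
| 10% | 72.9% | 70.0 | 210.0 | 120 |

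Independence is the unfavourable assumption. If everyone who misses an interim visit is also among those lost by 6 months, complete cases stay at 86.4 in every row.

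**Relative effect on power.** The article gives no effect size, so 87 itself cannot be reproduced. If 87 is read as the total of a two-arm comparison (43.5 per arm, two-sided), the implied difference is 0.33 × (1.960 + 0.842) × √(2/43.5) = 0.198 mmol/L. With that difference, power is 79.7% at 86.4 complete cases, 77.1% at 81, 75.6% at 78 and 71.0% at 70. These figures ignore clustering and any gain from repeated measures. They show relative loss, not the trial's true power.

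**Bias, by illustrative simulation.** Assumed: correlation 0.6 between visits, 5% missed at 3 months, 6-month loss of roughly 6 to 9% per arm, random in control and related to outcome in the intervention arm.

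- Loss depending on the observed early change: a true difference of −0.197 became −0.208 with complete cases and −0.197 with likelihood on all available visits.
- Loss depending on the unseen 6-month value: a true −0.198 became −0.214 and −0.208 respectively. The bias was reduced, not removed.

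**Loss of a whole village.** The Discontinuance section allows the research to stop in a single village. If that happened after the 3-month visit, the planned analysis would discard all 24 participants there, half of the 48 in one arm of that country, despite up to three measured visits each.

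**The case against.** The strongest reply is that the article never says it will analyse complete cases only. It is a condensed account, and a fuller plan might impute before the ANOVA. That stands as a caution. But the method is stated, not omitted, and its conventional form has this consequence; a fuller plan would have to add imputation or change the method to avoid it.

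A reader might also infer that the 10% allowance is shown to be inadequate. The documents do not support that. They give no rate of missed interim visits, and if the only missing data are from people lost by 6 months, 86.4 per country remain and the allowance essentially does its job. At 2% per interim visit, 96 × 0.90 × 0.98² = 83.0 remain, with power of 78.1% on the basis above.

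A reader might further infer that the people excluded are the less engaged ones, or that the 14-of-18 session rule restricts the analysis. Neither is supported. Assessments are separate from sessions and are done by health professionals in both arms. The session rule in the Process evaluation section defines programme completion, not an analysis set. Nor does a different rate of missing visits between arms bias the comparison by itself, if missingness is random within arm.

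Finally, a mixed model without a village term would still treat villagers as independent. That objection is right, and the village effect belongs in the fix.

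**Conclusion.** The point holds in a limited form. The named analysis conventionally excludes anyone missing one of four visits, while the sample size provides only for loss at 6 months and has no margin. On the plan's own 10%, about 29 of 288 participants would leave the interim comparisons, including those measured at those visits. Any further shortfall against 87 per country is conditional: about 86, 81, 78 or 70 complete cases at an assumed 0, 3, 5 or 10% absent per interim visit, if absences are independent of each other and of 6-month loss, and none beyond 86 if they coincide with it.

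It would go too far to say that an all-available-data model removes bias. It is valid when missingness depends on observed data, a weaker requirement than complete-case analysis makes, and otherwise may only reduce the bias. It retains interim data, but about 86 of 96 per country would still be the number with a 6-month value.

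**What to change.** Replace the repeated-measures ANOVA with a linear mixed model fitted by likelihood to all available visits. Include arm, visit and arm-by-visit terms, a participant effect and a village random effect, with small-sample inference suited to 12 villages. Analyse participants in the arm to which their village was randomised, and report missingness by arm and visit.

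The cost is revised analysis wording and slightly more analysis work, mainly for the village effect and its small-sample inference. No extra data are collected and no one else is recruited.

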## Methods/Design

### Study design

The ’Live More’ program will be evaluated using a cluster randomised controlled trial. The study design is illustrated in Fig. 1. The 6-month intervention will be conducted in three Pacific Island countries: Solomon Islands, Vanuatu and Fiji. In each country there will be two intervention villages and two control, resulting in a total of six intervention villages and six control villages across the three countries. Assessments will be conducted at baseline, and repeated at 30 days, 3 months and 6 months post baseline. The design, conduct and reporting of this study will adhere to the Consolidated Standards of Reporting Trials (CONSORT) guidelines for group trials.

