### Village eligibility criteria and randomisation

A village will be eligible to participate in the study if there is:an expressed endorsement and positive commitment by the village chief/community leader;observable overweight in the community (estimation of at least 40 % as observed by the ADRA Supervisor);relatively low literacy rate/education level in the potential participants as indicated by the community leader;adequate interest by residents who meet the participant eligibility criteria (described below) to achieve the required cluster sample size (described below);willingness to participate in the study as either a treatment or control site.

Once eligible villages are identified, ensuring they are not in immediate proximity to each other to avoid cluster contamination, the villages in each country will be randomised to either intervention or control by a researcher not familiar with the geographic location or nature of the village. Figure 1 shows the sequence for allocation of sites to treatment and control conditions.

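### Villages are randomised, but the only outcome analysis named is a participant-level repeated-measures ANOVA; with any within-village correlation of change, its between-arm comparisons exceed the nominal 5% error rate

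*Protocol article*

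**What the plan says.** **Design.** Under Study design, the program "will be evaluated using a cluster randomised controlled trial". Under Village eligibility criteria and randomisation, "the villages in each country will be randomised to either intervention or control". The layout is two against two villages per country, "resulting in a total of six intervention villages and six control villages across the three countries". Power calculation gives "two intervention villages each with 24 participants and two control villages each with 24 participants" in each country.

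**Analysis.** Statistical methods names three procedures, all judged at P < 0.05:
- For baseline differences between the arms, by country: chi-square "for categorical variables and independent samples t-tests for continuous variables".
- For change over baseline, one, three and six months: these changes "will be assessed using Analysis of Variance (repeated measures").

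The article contains no village effect, village-level summary, cluster-robust standard error or ICC. The sample size also has no allowance for clustering: it goes from 87 to 96 per country through 10% loss alone.

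**The concern.** When villages are allocated, the evidence about the program lies in the differences between intervention and control villages. An analysis whose error term is built from participants measures the wrong variation. The repeated-measures structure accounts for the same person being measured four times. It does nothing about 24 people in one village changing together.

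Such correlation is to be expected here. Program facilitators and Intervention describe facilitators drawn from each intervention village and sessions held as a group with shared discussion and action planning. A facilitator pair that works well, or badly, moves a whole village.

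If this is ignored, ordinary variation between villages can be reported as a program effect. The Discussion says that the findings will guide delivery of the intervention in the South Pacific, so a false positive would have consequences.

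**Working it through.** **Inputs from the protocol article.** Villages randomised within country; 2 v 2 per country, 6 v 6 in all; 24 per village, or 24 × 0.9 = 21.6 (about 22) after 10% loss; alpha 0.05, taken as two-sided because the article does not say; SD 0.33 mmol/L for triglycerides.

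**Assumed.** The ICC, shown from 0.01 to 0.10, because the documents give none.

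**The plan's own figure.** The 87 per country cannot be reproduced, because no target difference is stated. With 43.5 per arm, SD 0.33, two-sided 5% and 80% power, it corresponds to a difference of 0.33 × (1.960 + 0.842) × √(2/43.5) = 0.198 mmol/L. The step to 96 is 87 × 1.10 = 95.7. No design effect enters.

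**Participant-level comparison of change.** With m people per village, the design effect is DE = 1 + (m − 1) × ICC. The true standard error is √DE times the one used, and the true size of a nominal 5% test is 2 × [1 − Φ(1.96/√DE)]. For example, at m = 24 and ICC 0.05: DE = 1 + 23 × 0.05 = 2.15, √2.15 = 1.466, 1.96/1.466 = 1.337, size 18.1%.

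| ICC | DE, m = 22 | size | DE, m = 24 | size | SE ratio, m = 24 |
|---|---|---|---|---|---|
| 0.01 | 1.21 | 7.5% | 1.23 | 7.7% | 1.11 |
| 0.02 | 1.42 | 10.0% | 1.46 | 10.5% | 1.21 |
| 0.05 | 2.05 | 17.1% | 2.15 | 18.1% | 1.47 |
| 0.10 | 3.10 | 26.6% | 3.30 | 28.1% | 1.82 |

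Simulation (20,000 runs, m = 24) agrees: 7.9 / 10.5 / 18.8 / 29.1% with 2 v 2 villages and 7.9 / 10.3 / 18.0 / 28.7% with 6 v 6. Pooling the countries therefore does not cure it. A t-test on village means held 4.7% to 5.1% in the same runs.

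**Repeated-measures ANOVA, group-by-visit F-test.** Four visits, 22 per village, 4,000 null runs, with the village-by-visit share of within-person variance set to the value shown:

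| Share | 2 v 2 | 6 v 6 |
|---|---|---|
| 0 | 5.2% | 5.1% |
| 0.01 | 9.8% | 9.1% |
| 0.02 | 15.2% | 14.1% |
| 0.05 | 29.7% | 28.2% |
| 0.10 | 49.5% | 47.1% |

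**Degrees of freedom once villages are the unit.** Within a country: 4 villages − 2 arms = 2 df, critical t 4.30. Pooled with country in the model: 12 − 1 − 1 − 2 = 8 df, critical t 2.31.

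**Power at the back-solved 0.198 mmol/L, ICC 0.05, DE 2.15.** Noncentrality is 0.198 / [0.33 × √(2 × 2.15/n)] with n per arm. Within a country (n = 43.5) it is about 1.91, giving about 20% power on 2 df. Pooled (n = 3 × 43.5 = 130.5) it is about 3.31, giving about 82% on 8 df. Pooled power is about 97% at ICC 0.01 and 65% at ICC 0.10.

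**The case against.** **No between-arm outcome test is spelled out.** Statistical methods speaks of the extent of change and names neither a group factor nor a group-by-visit term. That is so, and the error-rate argument presupposes such a comparison. A controlled trial has to make one, however, and the ANOVA is the only tool named for it.

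**The t-tests and chi-square tests are for baseline only.** This stands. A reader might take them as planned outcome tests; the text does not support that. The first table describes a generic participant-level comparison of change, and the second the F-test of the ANOVA.

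**The size depends on an ICC that nobody has stated.** This also stands. A reader might infer that the 5% level is certainly broken, but the documents show only that it is broken if the relevant correlation is above zero. For change, that is the correlation of change within villages, which may be smaller than that of levels, since a village effect that is constant over visits cancels.

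**The reasons for correlation can be overdrawn.** Village facilitators and group sessions exist only in the intervention arm; Control villages describes printed material and an invitation to ask questions. A common food supply is not stated, and Outcome measures says that equipment is the same at each time point, not that each village has its own.

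**CONSORT.** A reader might say that the ANOVA breaches the promise that "The design, conduct and reporting of this study will adhere to the Consolidated Standards of Reporting Trials" for group trials. The guideline's content is not in the documents, so that is not claimed.

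**A fuller plan may add a village term.** This carries little weight. The article does not leave the method open: it names one that does not fit the design, and the sample size leaves out clustering too.

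**Conclusion.** The point holds: the stated outcome analysis does not match the stated unit of randomisation. It is conditional on non-zero within-village correlation of change, and on the ANOVA being used to compare the arms. Over the assumed ICC range the excess runs from modest (7.5% to 10% in place of 5%) to severe (above a quarter for a simple comparison of change, up to about half for the F-test). The ANOVA figures also assume village-by-visit effects that are independent from visit to visit. Because every between-arm P-value and confidence interval is affected, this should be settled before the data are analysed.

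**What to change.** Replace the repeated-measures ANOVA with a linear mixed model pooled over the three countries: random effects for village, village-by-visit and participant; fixed effects for arm, visit, arm-by-visit and country; and a small-sample degrees-of-freedom method. A simpler alternative, not an equivalent, is a country-adjusted comparison of the 12 village mean changes on 8 df. Report the ICC with the results. State that the formal comparison is pooled and that country-specific results are descriptive.

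**Cost.** No new data are needed. Intervals will be wider. The larger price is that the sample size was set per country, while a valid comparison within a country has only 2 df. Formal inference therefore moves to the pooled 12 villages, and the article should say so openly. A village term corrects the error rate; it does not make up for the small number of villages.

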### Discontinuance of the research

Provision is made for the research to cease, at a village and/or country level, in the event that the successful completion of the project is jeopardised by:natural disaster,civil unrestirretrievable communication breakdown with village leadersin-country mismanagement of funds.

## Discussion

In this paper we described the rationale and study protocol for the’Live More’ lifestyle intervention targeting NCDs within villages in the South Pacific. To the authors’ knowledge,’Live More’ is the first lifestyle intervention using the Reflect approach targeting low-income countries, such as those found in the South Pacific.

Targeting low-income countries in the South Pacific is important because increased access to nutritiously poor imported foods, coupled with limited funds available to support the delivery of public health campaigns and health care services, are having deleterious health consequences [30]. Over the last two decades, poverty has been growing in some countries of the South Pacific, with Solomon Islands and Vanuatu now on par with Guinea, Burundi, Senegal and Bangladesh [29]. Indeed awareness of the association between NCDs and poverty is growing with the NCD Alliance, consisting of four international NGO federations, advocating for the recognition that NCDs are a major cause of poverty, a barrier to economic development and a global emergency [31].

While there is strong evidence that lifestyle interventions are effective in addressing NCDs in high-income countries [9–12], peak bodies such as the World Health Organization acknowledges that there are few evidence-based lifestyle interventions suitable for low SES communities [32]. More specifically, regarding the countries in this study, these interventions are sparse in Fiji, and non-existent in Vanuatu and the Solomon Islands [16]. Furthermore, where programs do exist, these are costly and have limited usefulness in the communities that have low literacy levels and limited access to technology.

Interventions that provide professional learning opportunities for facilitators who live with and can mentor participants in the same village may provide a valuable framework for sustainable practice. Utilising villagers as facilitators not only uses local resources but can also improve psychological well-being, self-efficacy and confidence, particularly where underemployment is prevalent [33]. In addition, community self-help that involves the whole community through the interest and awareness it creates can also contribute to its development as a whole [33].

The ’Live More’ program is an innovative intervention targeting participants at risk of NCDs in low-income communities. The strengths of this study include the opportunity to build self-sufficiency and autonomy within a community, the objective measures of various biometrics and PA, and the comprehensive multi-component intervention. The findings from the study will be used to guide delivery of a lifestyle intervention to improve health and wellbeing in the South Pacific.

